## Abstract

Scalable, effective interventions are needed to address poor diet, insufficient physical activity, and obesity amongst rising numbers of cancer survivors. Interventions targeting survivors and their friends and family may promote both tertiary and primary prevention. The design, rationale, and enrollment of an ongoing randomized controlled trial (RCT) (NCT04132219) to test a web-based lifestyle intervention for cancer survivors and their supportive partners are described, along with the characteristics of the sample recruited. This two-arm, single-blinded RCT randomly assigns 56 dyads (cancer survivor and partner, both with obesity, poor diets, and physical inactivity) to the six-month DUET intervention vs. wait-list control. Intervention delivery and assessment are remotely performed with 0–6 month, between-arm tests comparing body weight status (primary outcome), and secondary outcomes (waist circumference, health indices, and biomarkers of glucose homeostasis, lipid regulation and inflammation). Despite COVID-19, targeted accrual was achieved within 9 months. Not having Internet access was a rare exclusion (<2%). Inability to identify a support partner precluded enrollment of 42% of interested/eligible survivors. The enrolled sample is diverse: ages 23–81 and 38% racial/ethnic minorities. Results support the accessibility and appeal of web-based lifestyle interventions for cancer survivors, though some cancer survivors struggled to enlist support partners and may require alternative strategies.

## 1. Introduction

Given the high number of cancer survivors in the United States (over 16.9 million in 2019 [1]) due to improvements in early detection and treatment, new challenges emerge in terms of preventing second malignancies and common comorbidities and promoting quality of life (QoL) and healthy aging among survivors. Healthy diet, weight management, and physical activity can enhance the quality (and quantity) of life for cancer survivors and reduce their risk for developing secondary cancers; however, few cancer survivors meet the World Cancer Research Fund (WCRF) and American Institute of Cancer Research (AICR) recommendations for diet and physical activity [2]. Moreover, recent National Health Interview Survey (NHIS) data indicate that 34% of adult cancer survivors report no leisure time physical activity and 33% have obesity [3], which clearly demonstrates the need for effective, scalable lifestyle interventions in this population.

Past studies have reported changes in diet, physical activity and/or weight loss among cancer survivors, with most interventions delivered face-to-face or via print and/or telephone [4]. For example, in the RENEW study, tailored mailed print materials and telephone counseling produced significant improvements in diet quality, physical activity, and body mass index at 12 months among 641 older survivors of breast, prostate, and colorectal cancer with overweight and obesity, which were sustained at two-year follow-up [5,6]. However, higher reach, more cost effective, technology-supported strategies might be required to address a public health problem of this magnitude.

Website intervention delivery requires less staff time and training than face-to-face and telephone-based approaches; furthermore, the incremental delivery costs per participant is minimal. Promising results were reported in a recent review of web-based lifestyle interventions for cancer survivors [7]; however, most of the programs were only 6–12 weeks in duration and did not assess long-term behavior change. As cancer survivors experience unique health concerns, more support and engagement may be required to achieve long-term maintenance of lifestyle changes.

Enrolling cancer survivors with support partners could lead to more sustainable gains in health behaviors. A dyad-based approach, in which 68 inactive breast cancer survivors with overweight or obesity partnered with their adult daughters who had similar characteristics, showed promise in the daughters and mothers (DAMES) study (n = 136) [8]. The dyads who received the tailored, self-help, print materials experienced significant improvements in body mass index (BMI), weight, waist circumference (WC), and physical activity at 12 months, compared to control arm dyads who received standard, publicly available brochures on diet, exercise, and weight status. Building on this research, the current study seeks to combine both the advantages of web-based platforms and partner support by developing and testing the first (to our knowledge) dyad- and web-based lifestyle intervention for cancer survivors.

The current paper describes the rationale, design, and recruited sample for an ongoing efficacy trial of DUET (daughters, dudes, mothers, and others together), a six-month web-based lifestyle intervention to promote weight loss among cancer survivors with overweight or obesity and their chosen supportive partners. The central hypothesis is that cancer survivor and support partner dyads that are assigned to the web-based intervention will lose significantly more weight at six months than dyads in the wait-list control. We also expect that the intervention will result in more favorable changes in other measures of adiposity (e.g., BMI and WC), diet quality, physical activity, QoL, and physical functioning and performance, as well as related biomarkers (e.g., insulin, glucose, total and high-density lipoprotein (HDL) cholesterol, triglycerides, leptin, adiponectin, interleukin 6(IL6), c-reactive protein (CRP), and tumor necrosis factor alpha).

## 2. Materials and Methods

### 2.1. Overall Design

DUET is a single-blinded, 2-arm randomized controlled trial (RCT) that will test a 6-month, web-based lifestyle intervention against a wait-list control among 56 dyads. Each dyad is comprised of a survivor of an obesity-related early-stage cancer and their supportive partner, both of whom have obesity or overweight, are insufficiently active, and consume suboptimal diets. The main outcome (body weight) is assessed at baseline and 6 months, along with several other secondary outcomes. This trial was approved by the University of Alabama at Birmingham (UAB) Institutional Review Board (300003882/Approval date: 10-28-2019) and registered with ClinicalTrials.gov (NCT04132219).

### 2.2. Participant Recruitment and Eligibility Screening

A two-step recruitment process was undertaken whereby initial enrollment efforts targeted cancer survivors, and once interest and eligibility were established, efforts were directed towards enrolling appropriate partners. Survivors of obesity-related cancers with 5-year cancer-free survival rates of at least 70% (i.e., localized renal cancer, and loco-regional ovarian, colorectal, prostatic, endometrial, and female breast cancers) [9]. Adult survivors of these cancers were identified through the UAB Cancer Registry, as well as through a wait-list of individuals who had previously expressed interest in lifestyle interventions and provided their contact email address or telephone numbers. Letters of invitation were posted to registry-ascertained cases, and telephone calls or email messages were placed to individuals on the wait-list. The Love Research Army (https://drsusanloveresearch.org/love-research-army, accessed on 27 September 2021) also initiated a series of email “blasts” to its members, and a recruitment website was established (https://duet4health.org, accessed on 27 September 2021). Finally, individuals not meeting eligibility criteria or disinterested in other ongoing cancer survivorship studies were apprised of DUET.

Study staff provided telephone follow-up on recruitment mailings and contacts by placing up to six calls at various days and times. The study was explained and interested survivors were screened for eligibility. Inclusion and exclusion criteria were established to target survivors who were most in need and who could best benefit from a web-based diet and exercise intervention. Inclusion criteria were as follows: (1) BMI > 25 kg/m^2^ [10]; (2) vegetable and fruit intake <2.5 cups/day; (3) moderate-to-vigorous physical activity (MVPA) <150 min/week [11]; (4) completion of primary cancer treatment; (5) English speaking and writing; (6) educational attainment of 5th grade or higher; and (7) daily use of the Internet and mobile phone access. Exclusion criteria were few and limited to those who were already adhering to modified diets or enrolled in an exercise program, residing in assisted or skilled nursing facilities, or recently advised by their physician to limit physical activity and/or having health issues that might make participation in an unsupervised weight loss intervention unsafe (e.g., pregnancy, severe orthopedic conditions, end-stage renal disease, metastatic cancer or other cancers with poorer survival, paralysis, dementia, blindness, unstable angina, untreated stage 3 hypertension, recent history of heart attack, congestive heart failure or pulmonary conditions that required oxygen or hospitalization within 6 months) [12]. Once initial eligibility was established and cancer case status was verified by treating physicians of any self-referrals, the survivor was asked to identify a local support partner (preferably within a 10-min drive) and have them contact the research team for screening. Supportive partners were required to meet all inclusion/exclusion criteria, except for being a cancer survivor.

### 2.3. Study Protocol

The research team provided study overviews for eligible dyads and answered their questions via conference calls. Informed consent was obtained from all participants involved in the study and signed electronically (Adobe Sign^®^, San Jose, CA, USA). Participants completed baseline assessments and dyads were randomly and evenly assigned to study arms (DUET intervention or wait-list control) using a permuted block design (block size = 4). Participants complete assessments again at 6 months and then wait-list control dyads receive the DUET intervention.

### 2.4. DUET Intervention

The DUET web-based intervention was adapted from the previously mentioned tailored, mail-delivered dyadic DAMES intervention [8] and then expanded to meet the needs of a broader range of cancer survivors and support partners (i.e., not limited to post-menopausal breast cancer survivors and their biological daughters). Like DAMES, DUET was theoretically grounded and primarily based on the social cognitive theory (SCT) [13]; which posits that participation in health behaviors is determined by individual factors (e.g., self-efficacy, or confidence in the ability to exert control over one’s own behavior) and the social and physical environment (e.g., barriers, social support from friends and family). The DUET intervention targets key SCT constructs by providing participants with resources (i.e., Fitbits and Aria Scales) to track diet, exercise, and weight, and provides guidance on setting incremental goals. Such strategies build upon small successes with lifestyle change and thereby enhance self-efficacy. The DUET weekly sessions also directly address weight loss barriers that are common for cancer survivors, such as fatigue and stress, as well as barriers common across populations, such as time constraints, to address the needs of both partners.

To further bolster dyadic interactions to enhance social support, concepts from interdependence theory and the theory of communal coping were incorporated [14]. DUET emphasizes relational factors such as joint problem solving, commitment to relationship quality and upholding mutual goals to promote adoption and maintenance of health behaviors. Moreover, dyads receive guidance on supporting their partners (e.g., how to ask for and provide help). In total, the DUET intervention draws upon 38 of the 40 behavioral change techniques that are categorized by the CALO-RE taxonomy purported by Michie and colleagues to promote adherence to healthful diet and physical activity patterns [15]. The two exceptions to the taxonomy are formal motivational interviewing (MI) and fear arousal. Although some MI elements were incorporated into the website design and information on cancer risk and recurrence and comorbidity are presented, emotionally evocative images were purposely avoided given the already high levels of anxiety related to such outcomes among cancer survivors and their loved ones [16].

The website includes the following sections: My Profile, Healthy Weight, Healthy Eating, Exercise, Weekly Sessions, Tools, News You Can Use, and Team Support. All users are given instructions on using the website features and encouraged to call the research team with any problems or questions. Once logged in, participants can update personal information (gender, age, height, weight, diet, physical activity, and cancer history) in the My Profile feature and then access tailored content in the Healthy Weight, Healthy Eating, and Exercise sections. Participants pursue and track their weight, diet, and exercise using study-provided equipment (Fitbit^®^ Aria 2 digital scales and Inspire fitness trackers (San Francisco, CA, USA), Portion Doctor^®^ tableware (Portion Health Products, St. Augustine Beach, FL, USA) and exercise bands (Theraband Academy, Akron, OH, USA)). Dyads also are encouraged to work as a team and use the commercially available MyFitnessPal (https://www.myfitnesspal.com/, accessed on 27 September 2021) app to set goals and view progress; log-ins and data are tracked to assess adherence. Participants are cued via text messages to complete 24 weekly interactive diet and exercise modules in the Sessions section; sessions range from 10–20 min. See Table 1 for session topics.

The Tools section includes tracking forms, online calculators, planning guides, tip sheets, and other healthy eating and exercise resources. Summarized updates on recent findings from salient research on diet, exercise, and/or weight loss for cancer prevention and control is provided in the News feature. The Team Support page offers practical tips on how dyads can support each other to promote lifestyle change (e.g., active listening). Regular website usage is encouraged via text messages (three per week) and tracked to assess intervention adherence. Short Message System (SMS) Text Messages also are a key component of the DUET intervention. After an initial welcome message, text messages are delivered at a frequency of three per week over the course of the intervention for a total of 72 messages for intervention.

Intervention adherence is evaluated using a variety of means. Completion of sessions, as well as website logins/duration and text message receipts/responses, are all tracked. Moreover, the dyad provides permission for the research office to access secure Fitbit wireless API generated by the Inspire tracker and Aria scale. These data are downloaded by study staff at intervention completion and stored on the study server by ID number until analysis.

### 2.5. Assessments

Baseline and 6-month follow-up assessments are largely identical except that some demographic and health characteristics that are likely to be time invariant for an adult sample over the study period (e.g., race/ethnicity, marital and educational status, height) are self-reported only at enrollment. Originally designed to include home-based assessments, the DUET protocol was modified prior to recruitment to virtual assessments via Zoom^®^ (San Jose, CA, USA) in order to continue research activities during the COVID-19 pandemic. Assessors were trained and evaluated for accuracy prior to initiation; measures were evaluated for reliability, as well as validity with those collected in-person data that are featured in a separate report [17]. All Zoom^®^ sessions are recorded to increase accuracy for timed performance testing to reduce discrepancies resulting from variable transmission of sight and sound and allow for periodic quality assurance evaluations among assessors. Once assessors review these files, time the tests, log the data, and quality assurance tests are completed, the recordings are deleted. Virtual assessments are scheduled during times when both dyad members can participate and occur in tandem with one member of the dyad undergoing the assessment first and the other recording the encounter on Zoom^®^, and then vice versa. Dyads are asked to prepare by viewing videos on performance testing (https://youtu.be/lbxctNuOgLk, accessed on 27 September 2021) and dried blood spot (DBS) collection (https://youtu.be/lBPLS4PoHv4, accessed on 27 September 2021).

Supplies also are sent to the home of the dyad member in which assessments will be performed. Mailed materials include an 8′ length of cord and two stickers (to mark the distance for the 8′ walk and up-and-go performance tests), two orange soccer cones (to enhance virtual visualization for walk testing), and a 36″ vinyl tape measure and two stickers (to measure and guide step height for 2-min step tests). The mailing also includes duplicate supplies to cover the assessment needs of each dyad member: (1) programmed Actigraphs (Walton Beach, FL, USA) with activity/sleep logs; (2) DBS kits (903TM Protein Saver Card, 2 lancets, 2 non-stick gauze pads, 2 small adhesive bandages, 2 alcohol prep wipes, 1–5 × 3″ foil biohazard envelop with desiccant) to self-collect fasting blood samples (12 h or more); and (3) Two ribbons (4–1″ × 55″) and a felt-tip marker (to perform repeated measures of WC). A digital scale is sent if participants do not have one. In addition to the virtual assessment and bio-specimen collection, each dyad member completes an on-line survey and a 2-day dietary recall conducted by telephone at each time point. Details of specific measures are provided in Table 2.

As indicated and in addition to comorbidity, other potential moderators of the intervention’s effect on weight change, such as demographic factors, distance separating the dyad members (and dyad cohabitation vs. not), smoking status [30], and risk for depression (as measured by the PROMIS Cancer-Related Item Bank) will be explored [31]. Potential mediators of effect also will be studied and include specific SCT constructs directly targeted by the intervention (e.g., self-efficacy, social support, and barriers). Self-efficacy will be measured with a 20-item instrument (α = 0.70–0.88) for dietary weight management [32] and the 6-item Lifestyle Efficacy scale (α = 0.95) [33]. Social support for these lifestyle changes will be assessed using validated 5-point scales with acceptable test-retest reliabilities (r = 0.55–0.86) and internal consistencies (α = 0.61–0.91) [34]. Barriers will be captured using a list of 36 common barriers to a diet with reduced fat and sugar, and increased fruits and vegetable intake, whole grains, and exercise (cost, availability, time, etc.) [35,36,37,38].

Upon completion of the intervention both dyad members undergo separate telephone debriefings on the acceptability and satisfaction of the various intervention components (e.g., website, equipment, text messages) and their suggestions for improvement are solicited.

As with any lifestyle intervention trial conducted in a high-risk patient population, especially one that is home-based and unsupervised, adverse events are a key concern. Thus, changes in health status of both study arms are systematically ascertained at study midpoint (3 months), in addition to 6-month follow-up. Any hospitalizations are logged, and admittance to the hospital resulting in an overnight stay, as well as events that are permanently disabling or life threatening are categorized as “serious” with attribution of the intervention explored further. Furthermore, all study participants are encouraged to call a toll-free study number to report any adverse events that occur between assessments.

### 2.6. Statistical Power

This 2-arm RCT formally tests for differences in the loss of body weight from baseline to 6-months that occurs among 56 dyads (with each dyad comprised of a survivor and a partner) who are randomized to two study arms. All other analyses and tests are exploratory. Power calculations are based on the following assumptions: (1) the retention rate will be identical to the DAMES trial (i.e., 90%), which is conservative as the duration for DUET is only 6 months instead of 12 months; (2) the eHealth intervention will promote weight losses of ~3.46 kg during the 6-month study period (similar to those observed in the Healthy Moves tailored-print, web-based, spousal support intervention—see companion article by Carmack et al. in this Nutrients edition [39]), whereas the control arm will be weight stable—a conservative estimate, since the average American gains 0.5–1 kg/year [40]); and (3) two-sided tests at an alpha level of 0.05 will be used. Given these assumptions, along with those of a two-sided two-group *t*-test, a standard deviation of 4.6 kg (from Healthy Moves [39]), and a sample size of 25 dyads per arm (allowing for 90% retention of the initial 28 dyads per arm), there is at least 80% power to detect differences in weight loss of −3.72 kg or greater between the two arms.

### 2.7. Data Analyses

The primary analysis will be performed on an intent-to-treat basis using baseline to 6-month data. Arm differences in weight loss will be assessed using a mixed linear model which accounts for the covariance between the dyad members. Specifically, mixed models repeated measures analyses will be used to test differences between arms, the two time points, and the potential interaction between arm and time point simultaneously. An appropriate structure for the covariance matrix (e.g., unstructured) will be selected using the final data. Clinical and demographic covariates of interest will be included in these models. The Tukey-Kramer multiple comparisons test will be used to determine which pairs of means are significantly different. Overall cross-sectional comparisons of continuous variable at baseline will be performed using the two-group *t*-test to determine if there are any differences remaining between the arms after randomization. For categorical variables, comparisons between arms will be performed using the two-group chi-square test (or Fisher’s exact test if the assumptions for the chi-square test are not tenable). The strength of the relationship between pairs of variables will be examined using Pearson (or Spearman, if needed) correlation analyses. Distributions of continuous study variables will be examined using stem-and-leaf, box, and normal probability plots and the Kolmogorov-Smirnov test; any of these variables that deviate from a normal distribution will be transformed prior to analysis or will be analyzed using non-parametric methods such as the Wilcoxon rank-sum test.

Statistical tests will use an alpha level of 0.05 and will be two-sided. SAS software (version 9.4 or later; SAS Institute, Inc., Cary, NC, USA) will be used to perform all statistical analyses. Analyses of secondary outcomes will occur similarly, though analyses are exploratory, and as such will not be controlled for multiple testing. To identify predictor variables associated with program efficacy, e.g., social support (type, amount), self-efficacy, and risk of depression, logistic regression analyses will be used. Odds ratios, along with their corresponding two-sided 95% confidence intervals, will be obtained for all variables included in these models.

For our initial statistical analyses that focus on determining potential demographic and cancer-type differences between enrolled DUET cancer survivors and partners, between cancer survivors who express interest in the DUET intervention versus those who refuse or are unresponsive, and those who enroll in the RCT versus those not enrolled, two-group t-tests are performed for continuous variables such as age, and chi-square tests are performed for categorical variables, such as gender, race/ethnicity, residence in a rural- or urban-classified county, and cancer-type. These analyses are now complete, and the results are presented in the next section—findings that are integral in assessing program interest and to appropriately generalize the main outcomes of this trial upon its completion.

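### The repeated-measures model leaves baseline means free by arm, so it is essentially a change-score comparison: valid, but it gives up precision, mainly for the exploratory secondary outcomes

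*Protocol article*

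**What the plan says.** Section 2.7 (Data Analyses) plans a mixed linear model for weight that allows for covariance within the dyad. On the mean structure it says that "mixed models repeated measures analyses will be used to test differences between arms, the two time points, and the potential interaction" of arm with visit. The two visits are baseline and 6 months, so baseline is a response.

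Nothing in the section sets the baseline means equal across arms. On adjustment it says only that "Clinical and demographic covariates of interest will be included in these models", and calls these clinical and demographic; the baseline value of the outcome is not named. The arms are also compared at baseline by two-group tests "to determine if there are any differences remaining between the arms after randomization". The same approach carries over to the other outcomes: "Analyses of secondary outcomes will occur similarly, though analyses are exploratory".

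Section 2.3 (Study Protocol) places randomisation after the baseline assessments. Section 2.6 (Statistical Power) sizes the trial with a two-group t-test on weight loss, which is a change-score calculation.

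**The concern.** With two visits and a free arm effect at baseline, the arm-by-visit term compares mean change between arms. A change score subtracts the whole baseline value, as if baseline predicted follow-up with slope 1. When r is below 1 this adds noise. Because arms are allocated after baseline, any baseline difference between them is chance. The analysis may therefore either impose a common baseline mean or adjust for the baseline value, and both are at least as efficient in large samples.

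Chance imbalance matters too. With equal variances at both visits, and given an observed baseline difference D, the change-score contrast is expected to miss the true effect by (r−1)D; at r = 0.5 that is half of D in the opposite direction. The baseline tests describe such an imbalance but do not correct for it.

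What is at stake is precision in a trial of 56 dyads whose accrual is complete. The validity of the result is not at stake.

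**Working it through.** **Inputs from the article.** Section 2.6: SD of weight loss 4.6 kg, 25 dyads per arm analysed, two-sided alpha 0.05, 80% power at 3.72 kg. Table 3: BMI SD 5.8 (survivors) and 6.1 (partners).

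**Assumed inputs.** The article gives neither an SD for weight nor any r. At an assumed height of 1.65 m, 5.8 × 1.65² = 15.8 kg and 6.1 × 1.65² = 16.6 kg; the range used is 12 to 22 kg. For secondary outcomes, r = 0.4 to 0.9. Variances are taken as equal at both visits. As in section 2.6, n counts dyads; clustering within the dyad was not simulated.

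**1. The plan's own figure.** A two-sided t-test with n = 25 per arm, SD 4.6 and 48 df (noncentral t) has 80% power at 3.7201 kg. The stated 3.72 kg reproduces.

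**2. Is the interaction a change score?** In one simulated two-visit data set with complete data, the arm-by-visit estimate was −0.35654 (SE 0.24432). The difference in mean change and its SE were identical. The common-baseline model gave SE 0.2355. With 10% of follow-ups removed, the interaction was −0.2643 against −0.2641 for the completers' change score: almost the same, but not identical.

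**3. Variance ratio.** For outcome variance s², per participant:
- change score: 2s²(1−r)
- baseline-adjusted: s²(1−r²)
- ratio: (1+r)/2

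Estimating the slope costs a factor of about 1 + 1/(2n−4) = 1 + 1/46 = 1.022 at n = 25 per arm. Over 20,000 simulated trials at each r, the ratios were 0.76 at r = 0.5, 0.87 at 0.7 and 1.00 at 0.96. The asymptotic values are 0.75, 0.85 and 0.98; multiplied by 1.022 they become 0.77, 0.87 and 1.00.

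**4. Weight.** The change SD implies r = 1 − 4.6²/(2·SD²).

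| Assumed weight SD (kg) | r | (1+r)/2 | Detectable difference (kg) | Power at 3.72 kg |
|---|---|---|---|---|
| 12 | 0.93 | 0.96 | 3.65 | 81.4% |
| 16 | 0.96 | 0.98 | 3.68 | 80.8% |
| 22 | 0.98 | 0.99 | 3.70 | 80.4% |

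These are asymptotic. The slope cost of about 2% cancels most or all of the gain, as the simulated 1.00 shows.

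**5. Secondary outcomes.** The extra dyads that a change score needs for equal precision are 1/ratio − 1. The last column takes an effect that the change score detects with 80% power.

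| Assumed r | (1+r)/2 | Extra dyads needed | Power with baseline used |
|---|---|---|---|
| 0.4 | 0.70 | 43% | 92% |
| 0.5 | 0.75 | 33% | 90% |
| 0.6 | 0.80 | 25% | 88% |
| 0.7 | 0.85 | 18% | 86% |
| 0.8 | 0.90 | 11% | 84% |
| 0.9 | 0.95 | 5% | 82% |

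With the factor 1.022 the end ratios become 0.72 and 0.97, so the variance reduction at this sample size is about 28% to 3%.

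**The case against.** The strongest reply is that nothing is wrong. A two-visit mixed model tested by its interaction is a standard trial analysis, and it agrees with the t-test on weight loss used for the sample size. Section 2.6 makes weight the only formal test, and there the gain vanishes. This stands: it limits the point to an improvement for exploratory outcomes.

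A second reply is that a fuller analysis plan may constrain the baseline or adjust for it. That is possible, and the article does not exclude it. But the article states a mean structure, and the comment is on that structure, not on a missing detail.

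A third reply is that the equality with a change score is not general. This also stands. It is exact only with complete data and a saturated mean structure, and section 2.6 allows for 10% loss. If survivors and partners share one arm-by-visit term under an unstructured dyad covariance with unequal variances, the model weights the two roles; in one simulated data set it gave 0.515 against 0.459 for the simple difference in mean change. Hence the word essentially.

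A reader might also infer that two-day dietary recall, activity or biomarkers have low test-retest correlation. The article does not say so, and section 2.5 refers reliability to a separate report. Waist circumference and BMI may well correlate highly over time, as weight does. The secondary figures are therefore a range over assumed r.

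**Conclusion.** The point holds as a free gain in precision, not as a fault in validity. The stated model is essentially a change-score comparison and makes no use of the equal true baseline means that randomisation guarantees. For weight the loss is negligible: 1% to 4% of variance in theory, about none at 25 per arm. For exploratory secondary outcomes the possible reduction is about 30% to 5% asymptotically, and slightly less here. It depends on an r that the article does not give and on equal variances at both visits.

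A reader might infer that the primary analysis is biased or that the trial is undersized because of this choice. Neither is supported. The contrast is unbiased over randomisation with correct type I error; the bias in question exists only conditionally on an observed chance imbalance. The sample size is consistent with the analysis.

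**What to change.** Keep the dyad mixed model but drop the arm effect at baseline: one common baseline mean across arms for each member role, with the arm contrast at 6 months as the test. Leave the covariance over the two visits unstructured, which section 2.7 already gives as its example. Apply this mainly to the secondary outcomes, and to weight for consistency.

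An acceptable near-equivalent is to regress the 6-month value on arm, baseline value and role, with dyad correlation. It is not identical: it drops participants without a 6-month value, whereas the longitudinal model keeps their baseline data.

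The cost is one model term and no new data. Section 3 reports data collection as still under way with statistical analysis to follow, so at that point the change could be specified before results were seen.
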